**Discussion:**

We have combined central and peripheral motor activation methods for the first time, attempting to use BFRT in combination with rTMS intervention to recruit more motor units by increasing motor cortex excitability, thereby enhancing skeletal muscle motor ability under BFRT and examining the intervention effects on skeletal muscle mass and strength in postmenopausal women. This will provide a new paradigm for healthy intervention in the skeletal muscles of postmenopausal women.

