###### Cortical excitability

2.6.2.2.5

Cortical excitability was assessed via MEPs amplitude. Single-pulse transcranial magnetic stimulation (sTMS) was delivered to the primary motor cortex (M1) using the MagTD device at 100%–120% of each participant's resting motor threshold (RMT). MEPs were recorded from the right abductor pollicis muscle at rest, and peak-to-peak amplitudes were measured. Six consecutive pulses were applied at 5-s intervals, with the mean amplitude serving as the excitability index. To account for inter-individual variability, MEPs were normalized to baseline values. If baseline variability exceeded 15% between groups, analyses were adjusted using either stratification or ANCOVA with baseline MEPs as a covariate.

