### Sample size estimation

2.7

Sample size estimation was performed using G*Power 3.1. Based on a previous study (42), the effect size was conservatively estimated to be 0.65, to ensure a conservative and robust study design, we adopted a more cautious effect size of 0.4 in the final calculation. Assuming a one-way ANOVA with three independent groups (1:1:1), a significance level of 0.05 (two-tailed), and a desired statistical power of 0.95, the required total sample size was determined to be 42 participants. With an attrition rate of 20%, a total of 54 participants (18 per group) needs to be recruited.

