### Statistical analysis

2.8

All data were analyzed using SPSS Statistics version 26 (SPSS Inc., USA). Continuous variables are presented as mean ± standard deviation. Baseline characteristics were compared using one-way ANOVA for normally distributed data or the independent-samples rank-sum test/chi-square test for non-normal or categorical data. Intervention effects over time were assessed using two-way repeated-measures ANOVA (time × group) across three time points (baseline, post-intervention, and long-term follow-up). Significant interactions were followed by Bonferroni-corrected pairwise comparisons. Pearson correlation was used to explore relationships between changes in cortical excitability, serum biomarkers, and muscle mass or functional outcomes. Potential synergistic effects of rTMS and LI-BFRT were further evaluated using factorial ANOVA, with significance set at *P* < 0.05.

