Moreover, cerebral cortical atrophy, motor neuron apoptosis, and neuromuscular junction (NMJ) degeneration induced by aging are considered key factors in the occurrence of senile sarcopenia (29, 31). Therefore, when the effect of simple skeletal muscle training is limited, increasing the number of motor units from the perspective of activating the central nervous system may be a new approach to improving or enhancing the efficacy of exercise interventions for skeletal muscle mass and function in postmenopausal women. TMS regulates cortical plasticity through time-varying magnetic fields, inducing electric fields to stimulate target cortical regions. It has been widely used in the treatment of neurological and psychiatric disorders associated with excitatory dysfunction of the brain. Among these, rTMS is commonly used to modulate cortical excitability, which can be evaluated through changes in MEPs (33, 51). Research has shown that rTMS can significantly alter motor cortex excitability and plasticity, thereby improving limb motor function (35, 36). In sports training applications, it has also been found that high-frequency rTMS can increase motor cortex excitability (52), while low-frequency rTMS can decrease motor cortex excitability (53). However, there are no reported applications for interventions targeting individuals with reduced skeletal muscle mass and strength or sarcopenia, particularly postmenopausal women.

This study has several advantages. First, this study is the first to combine non-invasive brain stimulation with BFRT in postmenopausal women, using a dual-target strategy aimed at simultaneously activating central (motor cortex) and peripheral (musculoskeletal) pathways to promote muscle hypertrophy and strength in older women under low mechanical stress conditions. This provides new insights for healthy interventions targeting skeletal muscle in older women. Second, this study comprehensively assessed outcomes related to muscle structure (muscle CSA) and function (muscle strength, physical activity function) in postmenopausal women, as well as cortical excitability and blood-based neuromuscular biomarkers. This design facilitates the evaluation of intervention effects from multiple dimensions and may provide potential mechanistic insights into the interactions between neural plasticity and muscle adaptability in mixed intervention responses.

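### The exploratory Pearson correlations of change scores carry no term for randomised arm, so if run over all three arms they can show a link that does not exist within any arm (minor)

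*Protocol article*

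**What the plan says.** The protocol article, section 2.8, gives one sentence to the relation between marker change and muscle change: "Pearson correlation was used to explore relationships between changes in cortical excitability, serum biomarkers, and muscle mass or functional outcomes". It names no arm covariate, partial correlation or within-arm analysis. It also does not say that the three arms are pooled.

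The nearest adjustment is in section 2.6.2.2.5 (Cortical excitability). It allows stratification or ANCOVA with baseline MEPs, and only if the groups differ at baseline. That does not remove an effect of arm on the change in MEPs.

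The abstract's Discussion paragraph states the working hypothesis, which is to "recruit more motor units by increasing motor cortex excitability, thereby enhancing skeletal muscle motor ability under BFRT". The main Discussion says of the design as a whole that it "may provide potential mechanistic insights into the interactions between neural plasticity and muscle adaptability in mixed intervention responses".

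**The concern.** A Pearson correlation is bivariate and has no place for a third variable. Here the third variable is randomised arm, and the trial expects arm to move both sides of the correlation: rTMS should raise cortical excitability, and training, with or without rTMS, should raise muscle size and strength. If the arm means differ on both axes, the pooled scatter tilts even when MEP change says nothing about muscle change within each arm.

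At stake is how an exploratory result is read. A significant pooled r could be reported as a neural-to-muscular link when it shows only that the arms differ on two measurements.

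**Working it through.** **The plan's own figure.** The protocol gives no figure for the correlation analysis, so there is none to reproduce. Only its sample sizes and effect sizes are borrowed.

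**Inputs from section 2.7**
- Three arms: "Assuming a one-way ANOVA with three independent groups (1:1:1". Total 42 evaluable and 54 recruited, so 14 or 18 per arm.
- Two-sided alpha: "a significance level of 0.05 (two-tailed), and a desired statistical power of 0.95".
- Effect sizes: "we adopted a more cautious effect size of 0.4 in the final calculation", and before that "Based on a previous study (42), the effect size was conservatively estimated to be 0.65". Both are read as Cohen's f, the SD of the arm means divided by the within-arm SD.

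**Assumptions that the protocol does not supply**
- The same f applies to the marker change and to the muscle change.
- Within-arm SD is 1 for both.
- Within-arm correlation is exactly zero.

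**Step 1: population value of the pooled correlation.** With zero within-arm correlation, only the arm means contribute to the covariance:

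pooled r = c × f² / (1 + f²)

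Here c is the correlation between the two sets of arm means.

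- f = 0.4: f²/(1 + f²) = 0.16/1.16 = 0.138
- f = 0.65: f²/(1 + f²) = 0.4225/1.4225 = 0.297

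Take the arms in the order control, LI-BFRT, rTMS + LI-BFRT.

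- *Pattern A: rTMS shifts MEPs only, and training shifts muscle equally in both trained arms.* Marker means are proportional to (0, 0, 1) and muscle means to (0, 1, 1). Centred, these are (−1/3, −1/3, 2/3) and (−2/3, 1/3, 1/3). The cross-product is 2/9 − 1/9 + 2/9 = 1/3 and each sum of squares is 2/3, so c = (1/3)/(2/3) = 0.5.
- *Pattern B: rTMS shifts MEPs only, and muscle rises evenly over the three arms.* Marker means (0, 0, 1), muscle means (−1, 0, 1). The cross-product is 1 and the sums of squares are 2/3 and 2, so c = 1/√(4/3) = 0.866.
- *Pattern C: both variables follow the same arm pattern* (for example both evenly spaced). c = 1.

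**Step 2: how often the test is significant.** Trials were simulated under each pattern (20,000 to 40,000 runs per case). The pooled Pearson test (N − 2 df) was compared with the arm-adjusted partial correlation (N − 4 df), both at two-sided 0.05.

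| Pattern | f | Pooled r | Pooled, N = 42 | Pooled, N = 54 | Arm-adjusted |
|---|---|---|---|---|---|
| No arm effect | 0 | 0 | about 5% | about 5% | about 5% |
| A | 0.4 | 0.07 | 7% | 8% | about 5% |
| A | 0.65 | 0.15 | 15% | 18% | about 5% |
| B | 0.4 | 0.12 | 12% | 14% | about 5% |
| B | 0.65 | 0.26 | 39% | 48% | about 5% |
| C | 0.4 | 0.14 | 14–15% | 17% | about 5% |
| C | 0.65 | 0.30 | 50–51% | 62% | about 5% |

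Shifts chosen freely, in within-arm SDs, give similar values. With MEP 0/0/1.0 and muscle 0/0.8/0.8 the rates are 7.6% and 7.9%. With muscle 0/0.8/1.2 they are 15.0% and 17.6%.

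**Step 3: degrees-of-freedom cost of adjustment.** By Fisher's z, the correlation detectable with 80% power is tanh[(1.960 + 0.842)/√(N − 3 − k)], where k is the number of arm terms.

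- N = 42: 0.42 with k = 0, 0.43 with k = 2.
- N = 54: 0.37 with k = 0, 0.38 with k = 2.

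**The case against.** **Pooling is inferred.** Section 2.8 does not say it, and separate within-arm correlations would avoid the problem. An article may also leave such detail to a fuller plan. This stands as a limit on the point. But the sentence does fix a method, that method cannot hold an arm term, and an unqualified correlation is ordinarily run on the whole sample.

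**The effects are assumed.** This also stands. Section 2.7 gives no effect for MEPs or biomarkers, and it sets 0.65 aside in favour of 0.4. The higher rates need rTMS to add to muscle gain as well. If it moves MEPs alone, the inflation at f = 0.4 is small.

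**The analysis is exploratory.** It is labelled so, and the time × group comparisons do not depend on it. A reader might infer that the Discussion rests its mechanistic claim on these correlations. It does not: the sentence credits the design and says only that insights may follow. A reader might also infer that nothing else bears on the mechanism. That goes too far, because the randomised comparison of rTMS + LI-BFRT with LI-BFRT covers both MEPs and muscle, although it does not test the link between them.

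**Adjustment loses signal.** Arm adjustment removes the between-arm variation in MEPs that rTMS is meant to create. What remains is an observational association. In one illustration of genuine mediation (assumed slope 0.4, MEP reliability 0.5, MEP shift 1.0, training effect 0.5), detection falls from 48% to 24% at N = 42 and from 58% to 29% at N = 54. The pooled figures there include some arm confounding, but the loss is more than two degrees of freedom. For that reason neither version should be read as evidence of mechanism.

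**Hand and leg.** Because "MEPs were recorded from the right abductor pollicis muscle at rest", a reader might also question pairing MEPs with leg muscle area. That is a separate matter of preference and no part of this point.

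**Conclusion.** The point holds as a minor one. As written, the correlations have no arm term. If run over all three arms, they can be significant when the within-arm correlation is zero. At N = 42 to 54 the false-positive rate is about 7–8% (f = 0.4) to 15–18% (f = 0.65) when rTMS shifts only MEPs and training shifts muscle equally in both trained arms. It is about 12–17% to 39–62% when rTMS also adds to muscle gain. The arm-adjusted test stays near 5% throughout.

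These figures depend on pooling, on equal f for both variables and on zero within-arm correlation, none of which the protocol states. They show the direction of the distortion and its possible size, and do not predict what this trial will find. No primary or randomised comparison is affected.

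**What to change.** In section 2.8, make the main version of this exploratory analysis a partial correlation adjusted for randomised arm or, equivalently, a regression of outcome change on marker change plus arm. An unadjusted pooled r may be reported beside it, labelled as such. Describe both as association and not as evidence of mechanism.

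The cost is one or two sentences, two degrees of freedom and no new data. Adjustment also sets aside the between-arm variation in MEPs. The planned randomised group comparisons already address that variation, and showing the pooled r keeps it visible.

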### Randomization and blinding

2.4

Participants meeting the inclusion and exclusion criteria will be randomly assigned to the rTMS + LI-BFRT group, LI-BFRT group, and control group at a 1:1:1 ratio. The randomization sequence will be generated by an independent statistician using a computer program with block randomization to ensure balanced sample sizes across groups throughout the enrollment process. Group allocation results will be concealed in numbered, sealed, opaque envelopes, which are stored and distributed by researchers not involved in recruitment, intervention, or assessment to achieve allocation concealment. Outcome assessors and data analysts will remain blinded to participants' group assignments throughout the study. Researchers implementing the intervention are required to withhold group information during assessments.

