#### rTMS+LI-BFRT

2.5.2

Participants will undergo a 12-week intervention consisting of three sessions per week, each lasting 60 min, combining rTMS (20 min) and LI-BFRT (40 min). The rTMS protocol is as follows: stimulation intensity of 90% of the RMT, is applied to the primary motor cortex (M1) with a stimulation frequency of 10 Hz, each sequence lasting 10 s, and an interval of 50 s. A total of 1,000 pulses are administered to each hemisphere, resulting in a total of 2,000 pulses for the rTMS intervention. Immediately thereafter, the same exercise intervention as the LI-BFRT group was performed.

The RMT will be determined before the start of the intervention. Measurements and interventions were performed using a MagTD transcranial magnetic stimulator (Irid Medical Equipment New Technology Co., Ltd., Wuhan, China) equipped with an aimQ tracking navigation system. Signals will be amplified and band-pass filtered between 20 Hz and 1 kHz, with a sensitivity of 200 μV/div and a sampling rate of 5 kHz. Subjects were instructed to maintain complete relaxation of the target muscle during stimulation and confirm the absence of background activity via real-time EMG feedback. First, activate the MEPs monitoring module. Surface electromyography (EMG) of the abductor pollicis brevis muscle is recorded using dedicated electrode wires. Align the center of the “8-shaped” coil with the representative region of the cerebral cortex associated with the hand function, ensuring the coil is tangent to the skull surface at a 45° angle. Subsequently, sTMS to observe reactive movements in the affected fingers. The RMT is defined as the minimum magnetic stimulation intensity required to elicit MEPs greater than 50 μV in at least 5 out of 10 consecutive sTMS stimuli while the thenar muscle is in a relaxed state.

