#### Control group

2.5.3

Participants in the control group will not undergo any exercise intervention and will maintain their original lifestyle habits. However, they will participate in a 12-week health education course, once a week for 20 min per session, to learn about skeletal muscle and exercise health.

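### The planned factorial ANOVA cannot estimate rTMS × LI-BFRT synergy, because no arm receives rTMS without LI-BFRT

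*Protocol article*

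**What the plan says.** The Statistical analysis section (2.8) first sets out the main longitudinal model: "Intervention effects over time were assessed using two-way repeated-measures ANOVA (time × group) across three time points". Bonferroni-corrected pairwise comparisons follow if the interaction is significant. It then adds a separate step, at the 5% level: "Potential synergistic effects of rTMS and LI-BFRT were further evaluated using factorial ANOVA".

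The arms are fixed in Randomization and blinding (2.4). Women are "randomly assigned to the rTMS + LI-BFRT group, LI-BFRT group, and control group at a 1:1:1 ratio". Their content is in Section 2.5:

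- Combined arm (2.5.2): stimulation comes first, and then "Immediately thereafter, the same exercise intervention as the LI-BFRT group was performed".
- Control arm (2.5.3): "Participants in the control group will not undergo any exercise intervention and will maintain their original lifestyle habits". These women attend weekly health education.
- LI-BFRT arm (2.5.1): 40-minute training sessions, with no stimulation and no sham described.

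No section describes an arm that receives rTMS alone. The limitations in the Discussion do not mention its absence.

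**The concern.** Two treatments are synergistic when their joint effect exceeds the sum of their separate effects. Showing this requires the effect of each treatment on its own. The trial observes LI-BFRT on its own but never rTMS on its own, so the data cannot tell an additive effect from a synergistic one.

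The practical risk is a false claim. The plan promises a synergy test at the 5% level. If the analyst enters rTMS and LI-BFRT as two factors, whatever rTMS-related term is printed could be reported as that test, although it is only a comparison of two arms. Joint central and peripheral action is the trial's main rationale in the abstract and Discussion, so such a claim would carry weight.

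**Working it through.** **Inputs.** Three arms allocated 1:1:1 (Section 2.4), 18 per arm (Section 2.7), and the arm contents in Section 2.5. The plan gives no figure for the factorial analysis that could be reproduced. Its sample size is for a three-group one-way ANOVA and does not bear on this point.

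**Step 1: fill the 2×2 table.** Write R = 1 for rTMS, B = 1 for LI-BFRT, and μ with subscripts in the order R, B.

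| R | B | Arm | n | Mean |
|---|---|---|---|---|
| 0 | 0 | Control | 18 | μ00 |
| 0 | 1 | LI-BFRT | 18 | μ01 |
| 1 | 1 | rTMS + LI-BFRT | 18 | μ11 |
| 1 | 0 | none | 0 | μ10, not observed |

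**Step 2: define synergy.** The interaction is μ11 − μ10 − μ01 + μ00. It needs μ10, which no arm estimates.

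**Step 3: write the model.** With E(y) = a + r·R + b·B + i·R·B, the arm means are:

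- control = a
- LI-BFRT = a + b
- both = a + b + r + i

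Only the sum r + i can be recovered. Any split between the rTMS effect r and the interaction i fits equally well.

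**Step 4: check the rank.** For 54 rows (18 per arm), the columns [1, R, B, R·B] have rank 3 against 4 parameters. R·B equals R in every row. Appending the interaction contrast (0, 0, 0, 1) raises the rank from 3 to 4, so it lies outside the row space and is not estimable. With a hypothetical fourth, rTMS-only cell the rank is 4 and the interaction has 1 df.

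**Step 5: see what software does.** One data set of 3 × 18 was simulated with 0.5 SD for each treatment, and three models were fitted in Python:

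| Model | Residual sum of squares |
|---|---|
| R + B + R·B | 39.344 |
| R + B | 39.344 |
| three-level group | 39.344 |

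The nominal factorial model used 2 model df, the same as a comparison of three groups. It still printed coefficients of 0.294 for rTMS and 0.294 for the interaction. These are simply the add-on difference, 0.294 + 0.294 = 0.588, cut in half by the fitting routine. SPSS 26, the package named in Section 2.8, was not run. How it labels the terms may differ, but the lack of estimability does not.

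**Step 6: show the ambiguity in numbers (illustrative).** Take μ00 = 0, μ01 = 0.5 and μ11 = 1.0.

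- If μ10 = 0.5, the interaction is 1.0 − 0.5 − 0.5 + 0 = 0.
- If μ10 = 0, it is 1.0 − 0 − 0.5 + 0 = 0.5.
- If μ10 = 1.0, it is 1.0 − 1.0 − 0.5 + 0 = −0.5.

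All three situations give the same three arm means.

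**Step 7: see what the estimable rTMS contrast contains.** Combined-arm sessions are described as "each lasting 60 min, combining rTMS (20 min) and LI-BFRT (40 min" respectively). Over 3 × 12 = 36 sessions this is 36 × 60 min = 36 h, against 36 × 40 min = 24 h for LI-BFRT. The difference is 12 h at full attendance.

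**The case against.** The strongest reply is that this is a supplementary analysis. The stated aim at the end of the Introduction concerns the effect of the combined intervention, the sample size rests on a three-group comparison, and the time × group model does not depend on the factorial step. That is right, and it limits the damage: the primary comparison of arms survives. It does not make the stated analysis capable of answering its question.

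It can also be said that software will run a factorial ANOVA with an empty cell. That is also right. What fails is the estimation of the interaction, not the execution of the procedure. Output that looks normal makes a misreading more likely.

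Reading factorial ANOVA as time × group does not help. That model is listed separately, and it cannot isolate synergy either. Nor could an unseen analysis plan supply the missing cell.

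The missing sham and the extra session time are a separate matter from estimability: adding a sham to the LI-BFRT arm would leave the rank at 3. The 20 minutes are the stimulation session itself, so they are not 12 h of purely non-specific contact. Outcome assessors and analysts are also blinded under Section 2.4. These points stand as qualifications. The sham matters for how the remaining contrast is described, since participants in the two training arms would know whether they had a stimulation session.

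Finally, both replacement contrasts are already among the pairwise comparisons in Section 2.8. There, however, they depend on a significant interaction and are not named as the answer to the question about rTMS.

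**Conclusion.** The concern holds. With the three arms described, the rTMS × LI-BFRT interaction has zero degrees of freedom, and no increase in sample size changes that. The result rests only on the arm structure in Sections 2.4 and 2.5 and on the usual definition of synergy as departure from additivity. It needs no assumption about effect sizes or variances.

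The trial can estimate LI-BFRT minus control, rTMS + LI-BFRT minus LI-BFRT, and their sum. The second is the add-on effect of rTMS given LI-BFRT. As the article describes the arms, it is not sham-controlled. A significant result there would not show synergy. The sentence in Section 2.8 is wrong as written and should be corrected before any results are reported under it.

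**What to change.** In Section 2.8, delete the sentence on factorial ANOVA and synergy, and pre-specify two contrasts at Week 12, the end of the intervention:

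1. rTMS + LI-BFRT minus LI-BFRT, reported as the added effect of an rTMS package without sham control on top of LI-BFRT.
2. LI-BFRT minus control.

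Week 12 is a suggestion, since the article does not single out a time point. The same contrasts can be reported at Week 24. State that a three-arm design without an rTMS-only group cannot assess synergy, and add the missing rTMS-only and sham conditions to the limitations.

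The cost is wording only. No arm, visit or participant number changes, and the trial gives up only a claim it could not support.

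If synergy is essential, the alternative is a fourth, rTMS-only arm and a new sample size. For scale, take 18 analysed per arm, two-sided 5%, 80% power and a normal approximation. The detectable interaction with four arms is (1.960 + 0.842) × √(4/18) ≈ 1.32 SD. The detectable difference between two arms is (1.960 + 0.842) × √(2/18) ≈ 0.93 SD. Adding an arm of 18 would therefore make the interaction estimable but detect only a very large one.
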